#### Ecological Momentary Assessments

The first and last week of the study will include intensive ecological momentary assessments (EMAs). During these weeks, 3 times per day, participants will be sent 6 identical survey questions per day for 7 days, on a quasirandomized schedule. The first 5 questions will be “How X do you feel right now?” where X will be replaced with a specific affect descriptor from happy, calm, anxious, sad, stressed, and participants will be asked to rate each item. The final question is “Over the last few hours, who have you spent the most time with?” and participants will choose from alone, friends, family, spouse or partner, coworkers, and costudents. Finally, every day for the entire duration of the study, participants will be asked “In general, how have you been feeling over the last day?” once each morning.

#### Analysis Plan

The first phase of the hypothesis-driven data analysis will be to process the raw data signals to derive interpretable features to test explicit hypotheses. The study will test a range of specific hypotheses and it would be beyond the scope of this paper to list them all. However, we present an exemplar here to demonstrate how such hypotheses could be tested. For example, 1 hypothesis that has been proposed in the research literature is that a key mechanism by which device use may affect mental health and well-being is by disrupting healthy sleep behaviors [30]. Specifically, it has been found that device use during the prebedtime period may delay sleep onset either by displacing sleep by device use or by increasing psychological arousal prior to lights out, thereby increasing sleep onset latency. In this study, estimates of device use (in the prebedtime period) will be combined with sleep features, including bedtime and rise time, time in bed, and total sleep time. Specifically, we will test whether the hypothesized mechanisms of change (ie, sleep) mediate the relationship between device use patterns and measures of the change (slope) in measures of mental health and well-being across the study period. Mediating effects will be tested using the strategies outlined by Hayes and Preacher [31], which are standard in behavioral research trials. Using linear structural equation models, support for mediation will be determined if measures of changes in measures of mental health and well-being become nonsignificant or are significantly reduced after controlling for the hypothesized mediating variable. We will assess the joint significance of the indirect pathways (ie, the joint significance of the pathways from the predictor to the mediating variable and from the mediating variable to psychiatric outcomes) using the bias-corrected bootstrap test and will also use the bootstrapping technique to test multiple simultaneous mediators [31].

The intensive longitudinal data on these features and self-reports of well-being will be subjected to data reduction techniques such as dynamic factor analysis, which are a set of techniques for estimating common trends in multivariate time series [32]. Dynamic factor analysis is a dimension reduction technique that aims to model a multivariate observed time series in terms of a finite number of common trends, with the aim of detecting the smallest number of trends that can summarize the data without losing information. The principle is the same as in other dimension reduction techniques, such as principal component analysis and factor analysis, except that the axes are restricted to be latent smoothing functions over time. The dynamic factor analysis will initially use data from the entire 4-week data collection period to examine the patterns of association between daily patterns of device use and daily variations in well-being and then will go on to examine the data from the two 1-week burst of intensive EMA to examine within-day covariation between patterns of device use and well-being. Variables that do not load on to 1 of the identified factors, but that are of strong interest as putative risk factors based on theory or previous empirical research, will be investigated in the statistical analyses as univariate predictors.

The second phase of the statistical analyses will consist of a number of analyses to be conducted to address the aims outlined above. A range of analytic techniques will be used, including ANOVA, specialized multilevel regression techniques that have been used in previous studies of intensive longitudinal data [33], and mixed Markov models [34]. These models are appropriate for testing the hypotheses with our aims, whereby changes in well-being across time can be considered an observed state switch and analyzed using observed Markov models (also referred to as manifest or simple Markov models or Markov chains [34-36]). These methods can also be used to investigate the temporal relationship between the intensive longitudinal data streams and the optimal time lag between these measurements and state switches (ie, the time lag between a predictor and the onset of a change in well-being status), which can be investigated by using higher order models, where the current state is modeled as depending on multiple preceding states [37].

We also plan to investigate the use of neural models to create machine-learned representations in our analysis. The intensive longitudinal nature of the data collection will enable large-parameter models to be trained using unsupervised and supervised machine learning techniques. Learning with self-supervision has recently attracted increasing interest as simple pretext tasks can be used to create versatile compressed representations of data. The main advantage of these embeddings is that they provide an initialization for downstream tasks. This is a more label-efficient mechanism to train supervised models. The benefits of unsupervised or self-supervised learning techniques studying human behavior are still relatively underexplored. However, the high dimensionality and the scale of the data described in this protocol lend themselves to this type of analysis. We plan to empirically test whether leveraging these methods has a positive impact on downstream predictive performance.

Given that participants are not required to complete all surveys, missing data will be handled via established imputation or multiple imputation techniques; however, we also plan to test machine learning–based imputation using autoencoders (eg, masked autoencoders). We expect that some partial data may be unusable, with the wearable devices adherence in intensive longitudinal studies is a known issue.

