Leveraging objective data from smartphones and wearables is needed to advance scientific research in this area. Physiological and behavioral biomarkers that can be measured by smartphones and wearables present a valuable way of identifying those at risk and measuring risk factors. Promising prior research has found that longitudinal smartphone and wearable data can be used to predict and, perhaps more importantly, complement existing clinical measures [7,10,11]. Indeed, the variables that can be captured by these devices can help us understand some of the most important determinants of health. For example, behavioral risk factors such as poor mental health, sleep, and physical activity are the greatest predictor of preventable illness and death [12], and nearly 8% of the US gross domestic product is lost to mental disorders each year [13]. However, mental and behavioral health conditions are complex and multifaceted phenomena, and measurement is nontrivial. Illness can manifest in a wide range of symptoms [14] that impact both physiological states and behavior. While there are examples of impressive longitudinal studies [7,15], the scientific literature on these topics is still dominated by studies with small and often unrepresentative samples, poor measurement of core constructs (eg, device use), self-reported measures of behavior that may not correlate with objectively measured end points, and a limited ability to address the psychological and behavioral mechanisms that may underlie the relationships between device use and well-being. For example, some studies focus solely on college students [15] or medical interns [7]. A number of recent authoritative reviews have made urgent calls for future research projects to address these limitations [7-9,16].

To address this gap in the literature, we have designed a large-scale intensive longitudinal study (the Digital Well-Being [DWB] study) to analyze the relationships among smartphone use, physiological and behavioral data from wearables and smartphones, and self-reported measures of mental health and well-being. We will recruit up to 14,000 participants who opt-in to complete intake and outtake surveys and daily ecological assessments and enable sensing of features from their smartphone. In addition, at least 50% (n=7000) of the participants will wear a smartwatch (Fitbit). Each individual’s participation in the study will be for 28 days.

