## Results

At the time of submission, the study infrastructure and app have been designed and built, the institutional review board of the University of Oregon has approved the study protocol, and data collection is underway. Data from 4182 enrolled participants have been collected as of March 27, 2023.

Table 1 shows the distribution of participants enrolled in the DWB study at the time of writing. We have been able to achieve a demographic split relatively similar to the 2021 US Census data [17] in terms of race, biological sex, age, and sexual orientation.

Figure 3 shows the geographic distribution of the participants based on home state. This map illustrated the geographic representation enabled by performing a study with our mobile platform and ubiquitous wearable and smartphone sensing.

**Table 1 table1:** Comparison between our study sample and the demographic breakdown of the US adult population. Statistics as of March 27, 2023.

Factor (level)		2021 US census [17], %		Digital Well-Being study, %

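### The mediation rule lets loss of significance after adjustment count as support on its own; this does not test the indirect effect and can disagree with the planned bootstrap

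*Protocol article*

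**What the plan says.** The Analysis Plan section sets out one worked mediation hypothesis: that sleep may "mediate the relationship between device use patterns and measures of the change (slope) in measures of mental health and well-being across the study period". It introduces this with the words "we present an exemplar here to demonstrate how such hypotheses could be tested".

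Two criteria follow in consecutive sentences.

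- First: "support for mediation will be determined if measures of changes in measures of mental health and well-being become nonsignificant or are significantly reduced". The comparison is between the models without and with the mediator.
- Second: "We will assess the joint significance of the indirect pathways", that is, predictor to mediator and mediator to outcome, "using the bias-corrected bootstrap test and will also use the bootstrapping technique to test multiple simultaneous mediators".

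The section does not say which criterion governs or what is concluded if they differ. Taken literally, the subject of the first sentence is the outcome measures, which cannot lose significance. The sentence makes sense only if it means the effect of device use on those measures, and it is read that way here.

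**The concern.** Write c for the total effect of device use on the outcome, c' for its effect after adjustment for the mediator, a for the path from device use to the mediator, and b for the path from the mediator to the outcome. In a linear model c − c' = a×b, so mediation is a question about a×b. A p-value moving from below to above 0.05 does not test that difference. If the mediator is correlated with device use, c' is estimated less precisely than c, and significance can be lost although b = 0. The article's own hypothesis, that device use displaces or delays sleep, implies a non-zero correlation.

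At stake is a mechanism claim of the kind sought under the sixth aim in the Introduction (which nondevice behaviors mediate). A behavior could be reported as a mediator because of collinearity while the interval for its indirect effect includes zero.

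**Working it through.** The article gives no error rate for the mediation rule, so there is no figure to reproduce. The check asks how often the loss-of-significance condition is met when there is no mediation.

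**Inputs.** From the article: the rule itself; n=7000 (Introduction, planned minimum with a Fitbit); n=4182 (Results, enrolled by March 27, 2023). Assumed, because the article does not give them: two-sided alpha 0.05; power for the total effect of 80%, 90% or 99%; correlation r between device use and mediator of 0.1 to 0.7; linear normal model; b = 0.

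**Formula.** Let L = 1.960 + z(power). With b = 0, the test statistic for c is N(L, 1) and that for c' is N(L√(1−r²), 1), with correlation √(1−r²) between them. Given z_c = x, z_c' is N(x√(1−r²), r²). The false-mediation rate is P(|z_c| > 1.960 and |z_c'| < 1.960). It depends on L and r only; n enters through L.

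**Numbers put in, 80% power.** L = 1.960 + 0.842 = 2.802.

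- r=0.3: √(1−0.09) = 0.954; standard error × 1.05; expected z of c' = 2.67
- r=0.5: √(1−0.25) = 0.866; standard error × 1.15; expected z of c' = 2.43
- r=0.7: √(1−0.49) = 0.714; standard error × 1.40; expected z of c' = 2.00

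**False mediation by loss of significance alone (numerical integration):**

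| Power for c | r=0.1 | r=0.3 | r=0.5 | r=0.7 |
|---|---|---|---|---|
| 80% | 1.3% | 5.8% | 14.4% | 30.5% |
| 90% | 0.9% | 4.0% | 11.2% | 27.3% |
| 99% | 0.1% | 0.8% | 3.1% | 12.7% |

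At r=0 the rate is zero. Regression simulation at n=7000 and 80% power (3000 runs) gives 5.6%, 14.5% and 31.2% at r=0.3, 0.5 and 0.7.

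**Either condition sufficient, as the rule is worded.** Take significant reduction to be tested by joint significance of a and b. The same simulation then gives 9.8%, 17.7% and 34.0%, against about 5% for joint significance alone.

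**Disagreement with the bootstrap.** With b = 0, 80% power, n=500, 1000 resamples and 1500 runs, significance is lost while the bias-corrected interval includes zero in 4.7%, 12.5% and 29.3% of studies at r=0.3, 0.5 and 0.7. The two can also differ the other way. With a = 0.3, b = 0.1 and c' = −0.03, the total effect is −0.03 + 0.3×0.1 = 0. At n=7000 the loss-of-significance condition is then met in 2.8% of studies, while joint significance of a and b is found in 100%.

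**Where the problem fades.** The standardized total effect is about L/√n. At 80% power this is 2.802/√7000 = 0.033, or 2.802/√4182 = 0.043. For larger effects:

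| n, standardized effect | L | r=0.1 | r=0.3 | r=0.5 | r=0.7 |
|---|---|---|---|---|---|
| 7000, 0.05 | 4.18 | 0.2% | 1.0% | 3.7% | 14.1% |
| 7000, 0.08 | 6.69 | 0.0% | 0.0% | 0.01% | 0.24% |
| 4182, 0.08 | 5.17 | 0.01% | 0.09% | 0.5% | 4.1% |

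**The case against.** The best defense is that a proper test of the indirect effect is already planned. The sentence on the bootstrap can be read as the formal version of the general description before it, and the section rests on a cited methods source. This softens the conflict but does not remove it: the first sentence says how support is determined and makes loss of significance sufficient, and nothing makes the bootstrap override it.

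Several stronger readings are tempting, and the document does not support them.

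- *The whole first rule is invalid.* It is not. Testing whether the effect is significantly reduced amounts to testing c − c' = a×b, which agrees with the bootstrap. Only the other condition fails.
- *False mediation claims are to be expected in general.* They are not. The rates of 14% to 31% need a total effect near the significance limit and a correlation of 0.5 to 0.7, and the article supplies neither figure.
- *The sixth aim is decided by this rule.* The text calls the analysis an exemplar, and the section also names multilevel regression and Markov models for the aims. It is, however, the only mediation rule stated, and it is put in definite terms.
- *The bias-corrected bootstrap is an error.* It is a recognized method. Its rejection rate with b = 0 is about 6.5% to 7% when path a has z of 3 to 4, and about 5% once z reaches 10. At n=7000, z of 3 to 4 means r of about 3/√7000 = 0.036 to 4/√7000 = 0.048, far below the correlations at which the loss-of-significance condition does harm.

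A fuller analysis plan may settle precedence. It could not do so without departing from the sentence printed here.

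**Conclusion.** The point holds in a limited form. As worded, loss of significance alone is sufficient for mediation, although it does not test the indirect effect, and it is not reconciled with the bootstrap criterion that follows. With alpha 0.05 and no true mediation, the false-declaration rate over r = 0.3 to 0.7 is 5.8% to 30.5% at 80% power for the total effect, 4.0% to 27.3% at 90% and 0.8% to 12.7% at 99%. It is about 1% or less at r = 0.1 with 90% power or more, and at most about 0.2% at n=7000 with a standardized effect of 0.08. The exposure is therefore to weak total effects and strongly correlated mediators. Power, alpha and r are all assumptions; the logical fault in the rule does not depend on them.

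**What to change.** In the Analysis Plan section:

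1. Delete the loss-of-significance condition and the or that follows it.
2. Correct the subject of the sentence to the effect of device use on the change measures.
3. State that mediation is supported only if the bootstrap confidence interval for a×b excludes zero, and apply this to each specific indirect effect in models with several mediators.
4. Report the total and direct effects with intervals, as description only.

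This costs about two sentences and no new data. With b = 0 and r = 0.3 to 0.7, deciding on the indirect effect alone brings the false-positive rate to about 4.5% to 5.2% by joint significance (n=4182 and 7000) or 4.8% to 6.5% by the bias-corrected bootstrap (n=500).

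Optional: use a percentile interval in place of the bias-corrected one. This matters only when path a is weak (z of about 2 to 6) and costs a little nominal power.

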The aims of the DWB study are manifold. We aim to (1) provide normative data on objective patterns of smartphone use and describe how these patterns of use vary with age, gender, geography, and functioning or mental health; (2) identify how patterns of smartphone use impact well-being and who is most vulnerable to harmful effects related to smartphone use; (3) identify groups of individuals who show similar patterns of covariation between smartphone use and well-being measures across time; (4) examine sociodemographic and personality or mental health predictors; (5) examine which patterns of smartphone use and well-being are associated with pre-post changes in mental health and functioning and compare the predictive capacity of these objective measures to relevant self-report measures (eg, smartphone addiction measures); (6) discover which nondevice behavior patterns (eg, sleep, physical activity, geographic movement, and social interactions) mediate the association between device use and well-being; (7) identify and explore recruitment strategies to increase and improve the representation of traditionally underrepresented populations; and (8) provide a real-world baseline of observed stress, mood, insomnia, physical activity, and sleep across a representative population.

Next, the methods used in our data collection protocol and preliminary statistics on the demographic profile of the first cohort of participants will be described.

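### The plan gives two mediation criteria that can disagree: loss of significance is sufficient for support, and nothing says that the bootstrap of the indirect effect decides

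*Protocol article*

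**What the plan says.** Aim 6 in the Introduction of the protocol article is to "discover which nondevice behavior patterns (eg, sleep, physical activity, geographic movement, and social interactions) mediate the association between device use and well-being". The Analysis Plan gives one worked case, sleep as mediator, to test whether it would "mediate the relationship between device use patterns and measures of the change (slope) in measures of mental health and well-being across the study period".

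Two criteria follow in consecutive sentences:

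- **Stated rule.** The criterion reads: "support for mediation will be determined if measures of changes in measures of mental health and well-being become nonsignificant or are significantly reduced". This applies once the mediator has been added to a linear structural equation model. Read literally, it is the outcome measures that lose significance; the device-use coefficient must be meant. The two arms are joined by an *or*, so either is sufficient.
- **Bootstrap.** The next sentence begins "We will assess the joint significance of the indirect pathways". It goes on to name the method: "using the bias-corrected bootstrap test and will also use the bootstrapping technique to test multiple simultaneous mediators".

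The language of determining support attaches only to the first. The second is described as something to be assessed. The article does not say which prevails when they disagree.

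**The concern.** Moving from p < 0.05 to p > 0.05 is not a test of the indirect effect. Adding any variable correlated with device use inflates the standard error of the use coefficient and moves the estimate by chance, so a modest effect can lose significance with no mediation at all.

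The stated rule also needs a total effect to start from and counts only a shrinking coefficient. Where the indirect effect opposes the direct effect, the total may be near zero and the coefficient grows once the mediator is added. Neither arm is built to register that.

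At stake is which behaviours are reported as mediators under aim 6. The same text plans several mediators at once ("will also use the bootstrapping technique to test multiple simultaneous mediators"), and several correlated variables take more precision from the use coefficient than one does.

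**Working it through.** **Inputs.** The rule and the bootstrap come from the Analysis Plan. The article gives no significance level, power, effect size or sample-size calculation for mediation, so there is no figure of the plan's own to reproduce. Sample sizes in the article: up to 14,000 participants, at least 7000 of them with a Fitbit (Introduction), and 4182 enrolled as of March 27, 2023 (Results).

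**Assumptions, not from the article.** Two-sided 5%; a standardised linear model; a single mediator; correlation r between use and mediator.

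**Step 1: what each arm tests.** Let a be the path from use to mediator, b the path from mediator to outcome, c' the direct effect and c the total effect. In a linear model c = c' + ab, so c - c' = ab. A test of the reduction is therefore a test of the indirect effect, counted in one direction only. Loss of significance compares two p values and does not involve ab.

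**Step 2: irrelevant mediator (b = 0).** The coefficient is unchanged in expectation (c' = c), but its standard error grows by 1/√(1 - r²). With noncentrality λ for the total effect, z_c ~ N(λ, 1) and z_c' ~ N(λ√(1 - r²), 1), with correlation √(1 - r²). Example: 80% power gives λ = 1.96 + 0.84 = 2.80; at r = 0.5, λ√(1 - r²) = 2.80 × 0.866 = 2.42. From 400,000 draws per cell, the probability that the total effect is significant and the direct effect is not:

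| Power for total effect | r = 0.3 | r = 0.5 | r = 0.7 |
|---|---|---|---|
| 50% | 6.8% | 14.4% | 25.2% |
| 80% | 5.8% | 14.4% | 30.5% |
| 90% | 4.1% | 11.3% | 27.5% |
| 99% | 0.8% | 3.2% | 12.7% |
| 99.99% | 0.0% | 0.1% | 1.8% |

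With four irrelevant, mutually uncorrelated mediators at r = 0.3 each (R² = 4 × 0.09 = 0.36), the rate is 18-21% at 50-90% power.

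**Step 3: raw-data check with the bias-corrected bootstrap**, b = 0, 80% power (n = 1000: 300 replicates; n = 4182: 150 replicates). The last column is the first plus the second minus the third.

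| n, r | Loss of significance | Bootstrap | Both | Either |
|---|---|---|---|---|
| 1000, 0.3 | 4.7% | 3.7% | 0.0% | 8.4% |
| 1000, 0.5 | 14.0% | 5.0% | 1.3% | 17.7% |
| 1000, 0.7 | 29.0% | 4.7% | 2.0% | 31.7% |
| 4182, 0.3 | 8.0% | 6.0% | 1.3% | 12.7% |
| 4182, 0.5 | 17.3% | 8.7% | 2.7% | 23.3% |
| 4182, 0.7 | 37.3% | 4.0% | 2.7% | 38.6% |

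The Monte Carlo standard error of the bootstrap column at n = 4182 is about 2 percentage points. The loss-of-significance column agrees with Step 2 within simulation error.

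**Step 4: opposing paths.** With ab = +0.03 and c' = -0.03, the total is c = 0.03 - 0.03 = 0.

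| n | Loss of significance | Bootstrap | Both |
|---|---|---|---|
| 1000 | 3.0% | 86.3% | 2.3% |
| 4182 | 6.7% | 100% | 6.7% |

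A second case at n = 7000 (a = 0.2, b = -0.1, so ab = -0.02; c' = +0.02) gives a significant total effect in about 5% of samples, loss of significance in 2%, and both indirect paths significant in 100%.

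**Step 5: the possible readings.**

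| Which criterion decides | Irrelevant mediators | Opposing paths |
|---|---|---|
| Stated rule alone | accepted at the Step 2 rates or more | largely missed |
| Either suffices | accepted at the Step 3 *either* rates or more | found by the bootstrap |
| Both required, taking only the loss-of-significance arm | 0-3% | found in 2-7% |
| Bootstrap alone | 4-9% | found in 86-100% |

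The words *or more* are needed because the simulations cover only the loss-of-significance arm. Adding the reduction arm by *or* cannot lower the rate of false support.

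**The case against.** A reader might infer that the plan has no valid test of mediation, so that irrelevant mediators are accepted and opposing pathways missed as a matter of course. The article does not support that. The reduction arm is, in a linear model, a test of the indirect effect. The next sentence plans a bias-corrected bootstrap of the indirect paths, extended to several mediators. Both harms occur together only if that bootstrap has no say; if either criterion suffices, only the first remains, and if both are required, only the second.

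The size can also be small. At n = 7000, 50-90% power corresponds to standardised total effects of only 1.96/√7000 = 0.023 to 3.24/√7000 = 0.039. An effect of 4.29/√7000 = 0.051 already has 99% power, where the rate is 0.8% at r = 0.3 and 3.2% at r = 0.5. At r = 0.3, even the 4-7% at lower power hardly differs from the bootstrap's own error rate. Exact cancellation is the extreme case of opposing paths.

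Nor do the aims name the separation of opposing direct and indirect effects. The Introduction's contrast of benefits and risks concerns patterns of use and kinds of people. Finally, the text is offered as an illustration ("we present an exemplar here to demonstrate how such hypotheses could be tested") in a condensed article, and a statistical analysis plan might settle the precedence.

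All of this limits the consequences and the severity. It does not rescue the loss-of-significance arm: that criterion is stated rather than left out, it is the only one to which a declaration of support is attached, and only the reading that gives it no role is free of its faults.

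**Conclusion.** The point stands as a conflict between two criteria, one of which contains an invalid sufficient condition. Loss of significance of the device-use coefficient should not count as support for mediation, and the article does not say that the bootstrap of the indirect effect decides.

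If the stated rule governs or either criterion suffices, the risk is false mediators. It is material when power for the total effect is moderate and the mediator correlates 0.5 or more with use, and small at 99% power unless the correlation is near 0.7. If the stated rule governs or both criteria are required, the risk is missed opposing paths. All rates rest on the assumed 5% level, linear model and correlations; none of these is given in the article.

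Severity: should-fix. The valid test is already planned, and the text is an exemplar for one of eight aims.

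**What to change.** Delete the sentence with the two-arm rule as a decision criterion. State instead that mediation is concluded only from the bootstrap confidence interval of the indirect effect (the product of the two paths), whatever the significance or sign of the total effect. Apply this equally to the analyses with several mediators. Report the indirect and direct effects with 95% intervals, and do not use the significance of the direct effect as a criterion.

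The cost is wording only: the bootstrap is already planned, and no further data are needed. Fewer mediators may be claimed.
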